#### 2.2.2. Target Population and Sampling

Recruitment commenced with a general inquiry of interest that was sent to child care centres across Nova Scotia that served children between the ages of 3 and 5 years with an enrolment greater than 20 children. The Department of Education and Early Childhood Development was instrumental in disseminating information about the research project to regulated child care centres throughout the province. Allowing for non-participation rates of 20%, we anticipated participation by 180 children across the intervention or control groups. As seen in previous research, this sample size of child participants is sufficient to have an 80% chance of detecting a 10% difference in physical literacy between the composite scores of the intervention and control group at the 5% significance level [39]. This sample should be sufficient to detect moderate between-group effects in fundamental movement skills [39]. Intra-class correlation (ICC) estimations were determined based on a similar study on preschool-aged children, which calculated an ICC of 0.02 [32]. Based on similar studies, we estimate moderate effect size on fundamental movement skills [40], and small-to-moderate effect size on physical activity [41].

Initially, 21 child care centres in Nova Scotia expressed interest in participating in the study and met study criteria. A visit was scheduled with the centres to meet with the director, further discuss the project, discuss and complete a survey, and view/photograph their designated outdoor play space and adjacent spaces if applicable. Two sites were excluded because they were advanced in their use of loose parts for outdoor play. Three other sites were excluded due to a low response rate to the invitation to participate. For efficacy, the minimum required for a centre to be involved was 10 children, and these centres only received parental consent for 3–5 children. This resulted in a final number of 16 centres in the original cohort, and 3 centres in the new cohort participating in the study. All children between the ages of 3 and 5 years attending the involved child care centres were eligible to participate in the intervention or control groups. Only children whose parents provided informed written consent were formally assessed. At the time of data collection, children also had to provide assent to participate in the assessment (e.g., agreeing to wear the accelerometer). Once the initial recruitment phase was complete and it was determined which centres met all the inclusion criteria (16 sites total), baseline data collection for children (movement assessment and accelerometer measurements) was completed in May 2017. The participating centres were then randomly assigned to the control or intervention group through computer based random number selections, based on rural and urban locations dispersed between the two groups. The full breakdown of number of centres and participants can be seen in Figure 3.

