### 3.4. Data Analysis

Descriptive statistics will be used to describe study participants (children, educators, parents) and participating child care centres. Linear mixed models with a random effect for centre will be used to determine if children exposed to the PLEY intervention had greater increases in physical literacy, PA, and time in active outdoor play, compared to children in the usual care group (control group). The model will include variables from the children’s TGMD-3 scores, PGMQ scores, and physical activity (as determined by accelerometry). The analysis will be approached from an intention-to-treat strategy. One of the primary outcome measures will be physical activity differences between the groups, while secondary outcomes include height, weight, BMI, and age. Additional analyses of the variables may include an analysis of covariance (ANCOVA) to determine differences in TGMD and PGMQ scores, with similar secondary outcomes of height, weight, BMI, and age, and again including a random effect to control for the clustered design. Missing data will be controlled for within the selected models and analyses. Significance level for these analyses will be set a *p* < 0.05.

Educator focus group data, and parent interview data, will be explored using qualitative analyses, to determine whether the intervention improved educators’ attitudes, beliefs, perceived competency, and intentions towards incorporating the intervention into practice; and increased parents’ and educators’ understanding of play in child health and development. These qualitative data will be transcribed and analyzed using NVIVO software to identify emerging themes. Children’s physical literacy and PA data will be examined in comparison with parent survey and interview responses, and educator survey and focus group responses, using a mixed methods approach. Data from the RE-AIM framework analysis and qualitative data emerging from the photo elicitation focus groups with intervention sites will determine the effectiveness of the intervention to achieve desired outcomes. The mixed methods approach will provide a more holistic understanding of the impact of the PLEY intervention on children’s physical literacy. Although the child measures only include some domains of physical literacy (e.g., physical competence and daily behavior) other aspects of the study including educator focus groups allow us to obtain data on the other components of physical literacy.

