## 4. Discussion

As the purpose of this paper is to describe the purpose, study design and methodology of the PLEY loose parts intervention, no results are included in this paper. It is hypothesized that children in centres exposed to the loose parts intervention will experience greater increases in physical literacy, PA and active outdoor play than the usual practice centres. Previous studies similar to this have reported changes (mean(95%CI)) of −0.2(−1.7 to 1.3) in physical activity between groups [53], and 2.5 (−1.7 to 6.7) in the sum of scores for fundamental movement skills between groups [40]. It is also hypothesized that parents and educators involved in the intervention centres will gain a greater understanding of physical literacy, PA, and active outdoor play. It is hypothesized that educators will be exposed to an increase of risk-taking behaviors with the introduction of loose parts into outdoor play environments and that they will begin to recognize their children’s ability to assess risk independently. Finally, it is also hypothesized that the loose parts intervention has the potential to clarify the role of the educator as a guide, a mentor and a co-player in outdoor environments.

This study consists of various strengths and limitations to be acknowledged. The major strength of this study lies in the uniqueness of an outdoor play intervention with the use of loose parts, the inclusion of urban, suburban, and rural regions of Nova Scotia, and in the measurement of child, parent and educator components. The limitations of this study include the dropout rate of children, which resulted in a lower sample size during the post-testing, and that not all components of physical literacy were measured as part of this study, given the age of the child.

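### The 80% power is quoted for 180 children and an undefined physical literacy composite, with no design effect or post-baseline loss shown and no power figure for physical activity

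*Protocol article*

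**What the plan says.** Section 2.2.2 expects 180 children after allowing 20% for non-participation. It claims that "this sample size of child participants is sufficient to have an 80% chance of detecting a 10% difference in physical literacy", measured as composite scores in the two groups, at the 5% level and cites a previous study for this. It adds that the sample should suffice for moderate between-group effects in fundamental movement skills (FMS). An intra-class correlation is then taken from a similar preschool study, "which calculated an ICC of 0.02", without a cluster size, a design effect, or a statement of how it entered the 180. On expected effects the section says "we estimate moderate effect size on fundamental movement skills [40], and small-to-moderate effect size on physical activity [41" (the numbers in brackets are the article's references).

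Sections 2.2.1 and 2.2.2 describe random allocation of centres: 16 in the first phase (8 and 8), and 19 in all (11 and 8) with 183 children at baseline. Section 3.4 analyses TGMD-3 scores, PGMQ scores and accelerometry with a random effect for centre, and states that "One of the primary outcome measures will be physical activity differences between the groups". Section 3.1.2 defines one summed score, total FMS, and assesses balance separately. The Discussion lists as a limitation "the dropout rate of children, which resulted in a lower sample size during the post-testing".

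**The concern.** There are three gaps between the power statement and the trial it describes.

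- **Outcome.** The 80% belongs to a physical literacy composite that no section defines. Physical activity, one of the primary outcomes, has only a verbal effect size.
- **Design.** The 80% is attached to a count of children, but the unit of allocation is the centre and the analysis carries a centre effect. The ICC is quoted, but its consequence is not shown.
- **Loss.** The 180 is the number left after non-participation. Nothing is set aside for children lost between baseline and post-test.

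What is at stake is how a null result is read. A reader who relies on section 2.2.2 could take a non-significant physical activity result as coming from a trial with 80% power. Over most of the effect range that the article itself expects, power for that outcome would be well below 80%.

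**Working it through.** **Inputs from the article.** 180 children; 5% level; 80% power; ICC 0.02; 16 centres (8 and 8), or 19 centres (11 and 8) with 183 children.

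**Assumptions.** Two-sided test; equal centre sizes; no gain from baseline adjustment; moderate = 0.5 SD; small-to-moderate = 0.2 to 0.5 SD; 20% post-baseline loss as a sensitivity value (the text gives no rate); ICC 0.05 as a sensitivity value.

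**1. Can the 80% be reproduced?** No. A 10% difference becomes a standardised effect only with a mean and SD, or a coefficient of variation, and none is given. One can only ask which effect 180 independent children detect with 80% power:

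d = (1.960 + 0.842) × √(2/90) = 0.418 SD.

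For a 10% difference this implies an SD of 10/0.418 = 23.9% of the mean.

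**2. Design effect with 16 centres.**
- Children per centre: 180/16 = 11.25
- DE = 1 + (11.25 − 1) × 0.02 = 1.205; effective sample size 180/1.205 = 149.4
- SE of the difference in SD units: √(1.205 × 2/90) = 0.1636

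With 20% loss: 144 children, 9 per centre, DE = 1 + 8 × 0.02 = 1.16, effective sample size 124.1, SE = √(1.16 × 2/72) = 0.1795.

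**3. Power.** Non-centrality is d/SE. The t reference has 16 − 2 = 14 df (critical value 2.145). For example, 0.418/0.1636 = 2.55 gives 66% by non-central t and 72% by the normal approximation.

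| Effect (SD) | 180 children: t / normal | 144 children: t / normal |
|---|---|---|
| 0.20 | 21% / 23% | 18% / 20% |
| 0.30 | 40% / 45% | 34% / 39% |
| 0.35 | 51% / 57% | 44% / 50% |
| 0.418 | 66% / 72% | 58% / 64% |
| 0.50 | 81% / 86% | 74% / 80% |

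The minimum detectable effect at 80% power (t) is 0.493 SD with 180 children and 0.541 SD with 144.

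**4. Sensitivity.**
- ICC 0.05, 180 children: DE = 1 + 10.25 × 0.05 = 1.51; power (t) 33% at 0.3 SD and 72% at 0.5 SD; minimum detectable effect 0.55 SD.
- 19 centres, 183 children, ICC 0.02: power (t) 68% at 0.418 SD and 83% at 0.5 SD. With 20% loss (146 children): 60% and 75%. The added centres change little.
- Baseline adjustment with an assumed correlation of 0.5 to 0.6 (variance multiplied by 1 − r², that is 0.75 to 0.64), 180 children, ICC 0.02: power (t) 78% to 84% at 0.418 SD and 50% to 57% at 0.3 SD.

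**The case against.** The strongest reply is that no arithmetic error has been shown. The 66% to 72% follows only if 180 was sized for independent children; the 0.418 SD is back-solved from that premise. The text does not say whether 180 already contains a design effect, the workings sit in a cited study, and a journal article may condense them. This stands. A reader might infer that the design fails to deliver 80%, but the documents do not support that.

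The article's other claim, that moderate FMS effects are detectable, holds at the quoted ICC before loss (81% at 0.5 SD). Baseline measurements exist and ANCOVA is mentioned, so adjustment could bring power at 0.418 SD back to about 80%; unequal centre sizes would pull the other way. Three centres were added partly to offset the loss of a centre and child withdrawals, so loss was not ignored. All of this stands too.

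Three further inferences are tempting and should be resisted:

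- **That physical activity is the sole primary outcome.** Section 3.4 calls it one of several, and the primary aim in section 2.2 also names physical literacy and active outdoor play. Powering on physical literacy is legitimate; the fault is that the composite is undefined.
- **That the prior results in the Discussion disprove the planned effects.** The −0.2 (−1.7 to 1.3) for physical activity comes from reference 53, whereas the expected effect rests on reference 41. For skills, "2.5 (−1.7 to 6.7) in the sum of scores for fundamental movement skills between groups [40" has an interval that includes zero, but with no SD its standardised size is unknown, so it does not contradict a moderate effect.
- **That the trial has a one-in-three chance on physical activity.** That needs an assumed 0.3 SD together with either 20% loss (34%) or ICC 0.05 (33%).

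The reply leaves three points unanswered: the undefined composite, the quoted ICC with no visible consequence, and a primary outcome without a power figure.

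**Conclusion.** The concern holds as a fault in what the power statement covers and shows. The 80% is unverifiable, because the composite has neither a definition nor an SD and no design effect appears. It would be about 66% to 72% if clustering was ignored, and 58% to 64% with an assumed 20% loss. On the article's own ICC the trial is sized for effects of about 0.49 SD, or 0.54 SD after that loss. A moderate FMS effect is therefore just covered before dropout and not after it. For physical activity, power reaches 80% only at the top of the expected range.

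These figures rest on a two-sided test, equal centre sizes, no baseline adjustment, and the stated readings of moderate and small-to-moderate. The loss rate is an assumption. The matter should be corrected because it governs how a null result is interpreted; it does not invalidate the design or the planned analysis.

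**What to change.** Replace the 80% sentence in section 2.2.2 with power or minimum detectable effects for total FMS and for physical activity, calculated for the clustered design. State the number of centres, the ICC of 0.02 and a higher sensitivity value such as 0.05, the number of children retained at post-test, a t reference based on centres, and any baseline-adjustment gain with the correlation assumed. Either define the physical literacy composite and give its SD, so that the 10% difference can be expressed as an effect size, or drop the 10% claim. If 180 already includes a design effect, show it.

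The cost is rewording and a short calculation. No extra enrolment is needed. The only downside is a stated power that may look less favourable.

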## 3. Procedure

### 3.1. Children

#### 3.1.1. Demographic and Body Composition

Demographic data, including age and sex, and physical characteristics, including height and weight, were taken by trained personnel at child care centres. Height was assessed using a portable stadiometer (SECA, Hamburg, Germany) and taken to the nearest 0.1 cm. Weight was assessed using a digital scale (A&D Medical, Milpitas, CA, USA) and taken to the nearest 0.1 kg. Children’s height and weight were measured with children wearing light clothing and no footwear. The height and weight of each child were used to determine Body Mass Index (kg/m^2^), which will be interpreted using z-scores. Data were collected at baseline, and at 3- and 6-months post-intervention.

#### 3.1.2. Physical Literacy

The Test of Gross Motor Development-3 (TGMD-3) was used to evaluate children’s fundamental movement skills (FMS) [42]. The TGMD-3 is a validated tool that measures gross motor ability development for children aged 3 to 11 years through a qualitative process-oriented approach comparing each child’s results to pre-determined standardized norms. The test is ideal for evaluating the success of motor skill interventions in this age group. A sum of all locomotor skills (run, skip, slide, gallop, hop, and jump) and object control skills (overhand throw, underhand throw, catch, dribble, kick, one-hand strike, two-hand strike) was determined, and used to calculate a total gross motor score (total FMS). Balance was assessed using the Preschooler Gross Motor Quality Scale (PGMQ), a validated tool which includes 4 balance measurements (single leg standing, tandem standing, walking line forward, and walking line backward) [43]. The assessment took a total of 15 to 20 min to complete. Each trained researcher/evaluator assessed one child at a time, going through the multiple performance criteria for each skill, and provided a score. The evaluator first demonstrated how to correctly perform the skill to the child, then asked the child to perform the skill. The children were given one practice trial, followed by two scored test trials.

#### 3.1.3. Physical Activity

Children’s PA was measured using accelerometry (ActiGraph wGT3X+; ActiGraph, LLC, Pensacola, FL, USA) during waking hours for nine consecutive days. In order to improve compliance and ensure data quality, parents were given an instruction sheet that explained how to attach the accelerometer over their child’s right hip and when the device was to be removed (night-time sleep, bathing/swimming). Parents and educators were also informed of the importance of consistent accelerometer wear to provide typical physical activity and sedentary behavior patterns. Accelerometer data were reduced and analyzed using ActiLife (Version 6). To improve comparability of data, accelerometer data collection and reduction decisions were consistent with a previous study of Canadian preschoolers [44]. Data were collected in 15 s epochs. Non-wear time was defined as ≥20 min of consecutive zero counts [44]. To be included in analyses, participants were required to have ≥4 days with ≥6 h of wear time each day [45]. A weekend day was not necessary for inclusion. Sedentary time was defined as ≤100 counts/min, light physical activity (LPA) as 100-1679 counts/min, and MVPA as ≥1680 counts/min [46].

### 3.2. Educators

#### 3.2.1. Go NAP SACC Outdoor Play and Learning Self-Assessment Instrument

The Nutrition and Physical Activity Self-Assessment for Child Care (Go NAP SACC) is an outdoor play and learning self-assessment tool that captures information on outdoor play time, outdoor play environment, education and professional development, and policy [47]. This tool was used to assess the outdoor environments of participating child care centres at baseline, and was completed by centre directors (CD) and/or early childhood educators (ECE). A total of 19 centers completed the survey; 16 from the original cohort, and 3 from the new cohort.

#### 3.2.2. Site Context Questionnaire

The site context questionnaire was developed to gather contextual information that was not captured through the Go NAP SACC instrument on outdoor play time, outdoor play equipment, outdoor play environment, centre policies, and loose parts materials. Specific questions were taken from the Environment and Policy Assessment and Observation (EPAO) tool [48], and others have been modified in a way that requires reflection rather than direct observation. The questionnaire was pilot tested with the former executive director of the Nova Scotia College of Early Childhood Education, to ensure the questions were appropriate for the intended audience. The questionnaire was completed by site directors, educators, and other centre staff during the intervention, and took approximately 20 min to complete.

#### 3.2.3. Educator Training Session

The full day educator training session was facilitated with the intervention sites after the baseline movement assessments and accelerometer measurements were completed. Seven of the eight intervention sites in the original cohort attended: 15 participants (13 ECEs and 2 CDs) took part in the training session; and an alternative training session was subsequently delivered to the one site (educator, assistant director and special needs coordinator) unable to attend the regular training session. In the new cohort, two training sessions were offered; 24 attended the first session, 21 attended the second session. Educators (preschool classrooms), support staff and centre directors were introduced to the project team, the goals, the research methodology and most importantly their role. Participants focused on the key components of the PLEY project including physical literacy and fundamental movement skills, active/outdoor play and loose parts, and the benefits of risk-taking in children’s play. This session also allowed for discussion among attendees from different child care centres to share experiences and stories that further informed the session. The training session was delivered through presentations and hands-on activities designed to promote the use of loose parts for active outdoor play, increase educator understanding of the importance of PA for young children, support observation and documentation, and explain the concepts of physical literacy. Educators had the opportunity to evaluate and describe photographs of children exploring loose parts and to “play” with the loose parts in an outdoor space. The loose parts kits were distributed to the intervention sites upon the completion of the training session. The session provided 6.5 professional development credit hours for the educators.

#### 3.2.4. Photo Documentation and Elicitation, and Focus Groups

Photo documentation and elicitation, and focus group sessions, were conducted at the 3-month and 6-month stage of the loose parts intervention. Photo elicitation involved participants photographing something specific prior to meeting with the research team for discussion of their photos; photo elicitation has previously been used to explore children’s health, physical activity, school environments, play and recreation [49,50,51,52]. This strategy/process for observing, documenting, and sharing stories of children playing with loose parts was designed to highlight and support the educators’ role in the intervention. The strategy, introduced at the training session, involved taking photographs accompanied by a documentation form focused on physical literacy, fundamental movement skills, and the educators’ role. Educators were asked to photograph, document, and submit examples of loose parts play that “caught their attention” as often as they could. Feedback, assistance and encouragement were made available throughout the intervention.

At the 3-month stage, all intervention participants were invited to attend a photo elicitation sharing and focus group activity to explore and share their experiences and to document changes they noted in their attitudes, beliefs, perceived competency, and intentions towards incorporating loose parts into the outdoor play environment. Each attendee (9 from original cohort; 15 from new cohort) was asked to bring a photo with documentation that demonstrated compelling evidence of how loose parts play supports physical literacy. The participants were organized into small groups (3 to 4 per group) to ensure that there would be opportunities for sharing between centres. Each focus group had a facilitator and a note-taker, and was audio-recorded. At the 6-month focus group sessions, both intervention and control centres were invited to participate. At the completion of these focus group sessions, the control groups received their loose parts kits.

During the photo elicitation sharing activity the educators described the play patterns of the children in the photos and highlighted how active play with loose parts helped children learn fundamental movement skills which supports their physical literacy development. The stories provided more context and allowed for better understanding of play in healthy child development. It was a catalyst for in-depth discussions and served to trigger comments from other participants about their own experiences. This activity was followed by a series of focus group questions divided into several categories: outdoor active play, loose parts, risk-taking, policies, and challenges/benefits of the intervention. These focus groups, which lasted approximately 45 to 60 min, allowed for more in-depth exploration of what made it challenging, or what assisted them in using the loose parts in their daily activities. On-site focus groups were facilitated for the two child care centres that did not attend the original session (4 educators).

